##### State-Trait Anxiety Inventory, Form Y (STAI-Y)

The State-Trait Anxiety Inventory, Form Y (STAI-Y), described in 1983, is one of the most widely used self-assessment scales in research and clinical practice [46]. This scale was adapted in French and validated in 1990, then called STAI-Y [47]. The STAI-Y is a test to assess momentary anxiety and habitual anxiety. The STAI-Y consists of 2 scales of 20 items each. The State-Anxiety scale assesses the feelings of apprehension, tension, nervousness, and anxiety that the subject feels at the time of the consultation. It is an indicator of transient changes in anxiety caused by therapeutic or aversive situations. The Trait Anxiety Scale assesses feelings of apprehension, tension, nervousness, and anxiety that the subject usually feels. The purpose of this scale is to identify anxiety as a stable arrangement. Both scales can be used independently. Each item in the inventory is rated from 1 to 4, depending on its intensity. The total score thus varies from 20 to 80. For ease of interpretation, the results are classified into 5 levels: (1) very high stress (≥ 66); (2) high stress (56 to 65); (3) medium stress (46 to 55); (4) low stress (36 to 45); (5) very low stress (≤ 35).

##### Depressive Experiences Questionnaire (DEQ)—Adolescent Version

Blatt and colleagues have developed an original line of reflection on the primary sources of depression, based on both psychoanalytical and cognitive work [48]. It was validated in French with a teenage version [49]. Depression could be either correlated with feelings of abandonment and impotence, weakness, and exhaustion, or with feelings of self-esteem, self-criticism, shame, and guilt. The DEQ is a self-assessment of 66 items to assess “depressive experiences” and thus differentiate anaclitic from internalization-introjection depressions. This notion of “depressive experience” refers to the existence of a depressive tone or depressivity, which can be demonstrated before the onset of clinical symptoms of depression and the constitution of a major depressive disorder.

##### Hospital Anxiety and Depression (HAD) scale

The Hospital Anxiety and Depression (HAD) scale is a self-administered scale of 14 items [50, 51]. It contains 7 questions related to anxiety and 7 other questions related to the depressive dimension, allowing the obtention of 2 scores. Each item is rated on a scale from 0 to 3, for a total maximum score of 21 for each score. A score between 0 and 7 is considered normal, a score between 8 and 10 shows symptoms of moderate intensity, a score between 11 and 14 highlights symptoms of average intensity, and finally a score between 15 and 21 corresponds to a high intensity of symptoms.

##### Ottawa Self-injury Questionnaire (OSI)

The Ottawa Self-injury Questionnaire (OSI) is a self-assessment questionnaire of 12 questions, assessing the frequency and topicality of self-mutilation, the context of the onset of the behavior, the physical areas involved, and the motivations for this type of behavior [52].

##### Eating Disorders Quality of Life (ED-QOL) scale

The Eating Disorders Quality of Life (ED-QOL) scale is a self-questionnaire comprising 25 items and 4 sub-scales: psychological, physical/cognitive, work/school, and financial fields [53]. A higher score indicates a better quality of life.

##### Exercise-Dependence Scale-Revised (EDS-R)

The Exercise-Dependence Scale-Revised (EDS-R) scale is used to measure 7 dimensions through 21 items with a 6-point Likert scale [54, 55]. These seven dimensions are as follows: tolerance, weaning, lack of control, reduction of other activities, intention, time, and continuity.

##### Evaluations of osteopathic treatment with SOAP (Subjective, Objective, Assessment, Plan) note form

The SOAP (Subjective, Objective, Assessment, Plan) note form is a validated, standardized and easy-to-use tool for assessing the evolution of somatic dysfunctions (sensitivity, mobility, texture, asymmetry) [56].

This tool is recommended by professional osteopaths in the context of osteopathic research and studies.

### Outcomes

#### Primary outcome

The primary outcome is the evolution of interoceptive sensitivity using the fMAIA scale (Multidimensional Assessment of Interoceptive Awareness). We will calculate the difference between the fMAIA values between the last and the first evaluations.

#### Secondary outcomes

Secondary outcomes are as follows:
Change in the patient’s overall clinical outcome (weight, pain, transit…) from T1 (baseline) to T3 (1 week after the last osteopathic session (group A) or 6 weeks after the first questionnaires (group B)).Change in the nature and severity of patient’s ED symptoms (EDDS and EDI-2) from T1 to T3.Change in the nature and severity of patient’s psychopathological symptoms (BSQ, BVAQ, RSE, STAI-Y, DEQ, HAD, OSI, EDS-R) from T1 to T3.Change in the perceived quality of life (ED-QOL) from T1 to T3.Change in somatic dysfunction (SOAP note form) from T1 to T3.Qualitative analysis of interviews of patients who received osteopathic treatment and osteopath students that performed the sessions (Interpretative Phenomenological Analysis method).

### Statistics

#### Sample size

To date, there is no quantitative data on which to base an order of expected effectiveness because this study is the first in the field. The calculation of the necessary number of subjects based on previous published research is therefore not possible. However, we carried out a clinical preparatory phase for the research by offering 3 osteopathy sessions of the initial treatment protocol to 3 patients with AN. They completed the MAIA questionnaire before and after the 3 sessions. For these 3 patients, total fMAIA values first and after evaluations were respectively 15.2 (sd = 7.9) and 23.2 (sd = 7.3) with an average difference of 7.97 (sd = 3.43). If the results of the study are positive, even if this sample size (*n* = 3) was too small to do statistical tests, that gave a favorable trend to support the study.

Finally, it seems essential that each of the two groups has more than 30 patients (use of parametric tests). Considering a 5 to 10% dropout rate, we calculated a sample size of 36 patients per treatment group.

In addition, this research is categorized as interventional research with only minimal risks and constraints mentioned 2 ° of Article L. 1121-2 of the Public Health Code. In this context, there are no anticipated formal stopping rules.

#### Statistical methods

##### Quantitative data

First, we will conduct descriptive analyses (calculations of means and standard deviation for the quantitative variables, percentages, and absolute numbers for the qualitative variables).

Quantitative variables will be analyzed with Student’s *t* test or a Mann-Whitney rank test if the validity conditions of the Student’s test are not validated. That will include the primary outcome as the difference between the fMAIA values between the last and the first evaluations, and the secondary outcomes such as the change in the patient’s clinical outcome (weight, pain…), the change in the nature and severity of patient’s ED symptoms (EDDS and EDI-2), the change in the nature and severity of patient’s psychopathological symptoms (BSQ, BVAQ, RSE, STAI-Y, DEQ, HAD, OSI, EDS-R), the change in the perceived quality of life (ED-QOL), and the change in somatic dysfunction (SOAP note form) from T1 to T3.

Qualitative variables will be analyzed with a chi-square test or an exact Fisher test if the validity conditions for chi-square are not validated. That will include the socio-demographic data and some secondary outcomes such as the change in the patient’s clinical outcome (localization of pain, transit…) from T1 to T3. Statistical tests will be two-sided with a significance level set at 0.05.

Relative to sample size, we did not plan any adjusted or additional analyses. In addition, we will collect different information for each patient at each stage of the protocol (inclusion, randomization, assessments). Subjects randomized to a group that will ultimately do not join their randomization group will be out of the study. We have estimated for the calculation of the sample size a dropout rate of 5 to 10%, which remains compatible with sufficient statistical power. We will compare the characteristics of dropout subjects compared to those who completed the study to investigate possible biases.

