#### Randomization

All patients who give consent to participate and who fulfill the inclusion criteria will be randomized. Randomization will be centralized and stratified according to the status of treatment at inclusion (outpatient care or hospitalization) and age (2 classes: 13–15 years old included and 16–20 years old). A randomization list with blocks of variable sizes will be computer-generated by a statistician independent from the group recruiting the patients and the group taking care of patients. The allocation ratio will be 1:1.

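### Sample size is given as the reason not to adjust the primary fMAIA comparison, but prespecified ANCOVA with baseline and the two stratification factors would be at least as precise for almost no cost

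*Protocol article*

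**What the plan says.** All references are to the Protocol article.

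- **Primary outcome:** "We will calculate the difference between the fMAIA values between the last and the first evaluations". The endpoint is the raw T3 minus T1 change.
- **Statistical methods, Quantitative data:** "Quantitative variables will be analyzed with Student’s *t* test or a Mann-Whitney rank test if the validity conditions of the Student’s test are not validated". This covers the primary outcome and the continuous secondary outcomes.
- **Same section, on adjustment:** "Relative to sample size, we did not plan any adjusted or additional analyses".
- **Randomization:** "Randomization will be centralized and stratified according to the status of treatment at inclusion (outpatient care or hospitalization) and age", with two age classes (13–15 and 16–20 years), hence four strata. Blocks vary in size and allocation is 1:1.

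Neither baseline fMAIA (other than by subtraction) nor either stratification factor enters any test.

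**The concern.** The protocol makes a decision on adjustment and gives a reason for it, and the reason is mistaken. Few patients would argue against a model with many covariates. They do not argue against three that are fixed in advance.

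Two consequences follow. First, a change score corrects for baseline with a fixed slope of 1, whereas ANCOVA estimates the slope. When r is below 1 and the SDs are similar, the slope of 1 over-corrects and adds variance. Second, the trial stratifies on treatment status and age and then leaves both out of the analysis. If they predict the change in fMAIA, the standard error does not reflect the balance that stratification has produced.

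At stake is precision in a trial with no stated target difference or power. The group size comes from wanting more than 30 per arm, so there is no known reserve.

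**Working it through.** **Inputs from the document.** 36 patients per arm; 5–10% dropout; two-sided 5% level; preparatory-phase SDs (n = 3) of 7.9 before, 7.3 after and 3.43 for the change.

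**Assumptions, not in the document.** The correlation r in the trial population (range 0.5 to 0.9 shown); equal SDs at T1 and T3 unless stated; a true difference of 0.6 SD of T3; block sizes of 2, 4 and 6.

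**1. The plan's own figure.** 32/0.90 = 35.6, rounded up to 36, and 34/0.95 = 35.8, rounded up to 36. So 36 per arm is consistent with more than 30 evaluable patients and the stated dropout. After dropout, 36 × 0.90 = 32.4 to 36 × 0.95 = 34.2 remain; I use 33. No effect size or power is given, so no power-based figure can be checked.

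**2. Variance, equal SDs (SD = 1).** Change score: 2(1 − r). ANCOVA: 1 − r². Ratio: 2(1 − r)/(1 − r²) = 2/(1 + r).

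| r | Change score | ANCOVA | Ratio |
|---|---|---|---|
| 0.5 | 1.00 | 0.75 | 1.33 |
| 0.7 | 0.60 | 0.51 | 1.18 |
| 0.9 | 0.20 | 0.19 | 1.05 |

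**3. The correlation implied by the preparatory patients.** r = (7.9² + 7.3² − 3.43²)/(2 × 7.9 × 7.3) = 0.90. With their own unequal SDs, ANCOVA residual variance is 7.3² × (1 − 0.901²) = 10.02 against 3.43² = 11.76 for the change, a ratio of 1.17. Three patients cannot fix r.

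**4. Power (noncentral t, 33 per arm, difference 0.6 SD, baseline adjustment only).**

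| r | t test on change | ANCOVA |
|---|---|---|
| 0.5 | 67% | 79% |
| 0.7 | 87% | 92% |
| 0.8 | 97% | 98% |
| 0.9 | about 100% | about 100% |

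Going from 64 to 61 degrees of freedom for three covariates leaves the ANCOVA figure at r = 0.5 at 79%.

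**5. Baseline imbalance.** If the arms differ by b at baseline by chance, T3 is expected to differ by r × b, so the change differs by (r − 1) × b. A share of (1 − r) stays in the estimate with reversed sign: half at r = 0.5, a tenth at r = 0.9.

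**6. Stratification factors.** Simulation with 64 patients, four strata, permuted blocks, r = 0.5 and 8,000 null runs per setting:

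| Share of change variance explained by strata | t test | Mann-Whitney | Strata-adjusted |
|---|---|---|---|
| 0% | 4.9% | 4.7% | 4.9% |
| 10% | 3.8% | 4.0% | 4.8% |
| 30% | 2.3% | 2.3% | 5.3% |

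If the factors instead shift T1 and T3 by the same amount, they cancel in the change. A separate simulation of that case (72 patients, 8% missing, 4,000 runs per setting) gave 4.7–5.6% for the t test, which is nominal.

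**The case against.** The strongest defence is that the trial calls itself exploratory, that the unadjusted comparison is valid under randomisation, and that the change score already uses baseline. At the only correlation the document supports, the gain from adjustment is small. All of this stands: the choice is inefficient, not wrong, and the size of the loss is unknown.

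Four stronger readings might be inferred, and the document does not support them:

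- **That a baseline imbalance passes in full into the result.** That describes a comparison of T3 values alone. Here baseline is subtracted, and only a (1 − r) share remains.
- **That ignoring the strata makes the p-value invalid.** Any error is conservative, and it arises only if the factors predict change. Nothing in the document shows that they do.
- **That T2 data on fMAIA are collected and thrown away.** The article schedules a second assessment, but the instruments given at each visit are in Fig. 2, which is not shown. T2 is also timed differently in the two arms (before the third session, or three weeks after the first questionnaires).
- **That the primary test is left open.** Groups above 30 were chosen so that parametric tests could be used, so the t test is the intention and the rank test a fallback. What remains is a minor point: the switch depends on conditions that are not defined and are checked on the data.

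An analysis plan that is not shown does not answer the point, because the article states the decision and its reason.

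**Conclusion.** The concern holds as a loss of efficiency that should be corrected. The justification by sample size is mistaken. Omitting baseline from the model costs 33% in variance at r = 0.5, 18% at r = 0.7 and 5% at r = 0.9 with equal SDs, or about 17% with the preparatory patients' own SDs. In power, at a 0.6 SD difference, this is about 12 points, 5 points and almost nothing at r = 0.5, 0.7 and 0.9.

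Confidence is high that the choice was made and that adjustment would be at least as good for practical purposes. It is low on the size of the gain, which rests on an assumed r and an assumed true difference. Any further gain from the stratification factors depends on their predicting change in fMAIA. There is no inflation of false positives.

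**What to change.** - **Primary analysis.** Prespecify a linear model (ANCOVA) of T3 fMAIA on group, baseline fMAIA, treatment status at inclusion and age class. Analyse patients with T3 data by randomised group, report the adjusted difference with a 95% CI, and drop the data-driven switch of primary test. Including patients without T3 would need a stated missing-data method; ANCOVA alone does not bring them in.
- **Sensitivity analyses.** Keep the unadjusted t test and the Mann-Whitney test here.
- **Continuous secondary outcomes.** Use the same model, with each outcome's own baseline.
- **Wording.** Amend only the part of the sentence that concerns adjusted analyses. Keep the commitment to no additional analyses, which guards against post hoc testing.
- **Reporting the gain.** If the change is justified by precision, show the range over r, not a single figure.
- **Optional.** A mixed model with T2 and T3 is possible only if fMAIA is collected at T2, and would have to deal with the different T2 timing in the two arms.

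The cost is a change of text. Treatment status and age are recorded for randomisation and baseline fMAIA is already needed for the endpoint, so no new data are required. The change should be made before any comparison by group is seen.

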#### Non-inclusion criteria

Patients will not be included in the study if (1) they are male, (2) they are under 13 years old or over 20 years old, (4) they have a contraindication to osteopathic body approach sessions (fracture, recent surgery, etc.), (5) they have a body mass index (BMI) < 14 kg m^−2^, (6) they need a naso-gastric tube, (7) they are in a “separation period”, (8) they are not fluent in French, (9) they are not covered by health insurance, and (10) they are part of another research protocol.

Non-included subjects will be listed along with the causes of their non-inclusion.

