#### Exclusion criteria

Patients will be excluded from the research if (1) they have a contraindication to osteopathic body approach sessions (fracture, recent surgery, somatic state not compatible with the osteopathic treatment), (2) they are not covered by health insurance, and (3) they are part of another research protocol. Excluded subjects will be listed along with the causes of their exclusion.

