#### Blinding

Only osteopaths, their accompanying persons, and a psychologist coordinator ([name]) will receive information about group allocation, as well as patients and parents when the patient is under 18. The assessor of the clinical and psychological outcomes (research psychologist) will be blinded from the treatment group and will use standardized research questionnaires. Assessors of the osteopathic outcomes will not perform the osteopathic sessions, to guarantee an independent evaluation.

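### The protocol removes randomised patients who do not take up their allocation, so the primary comparison is not by randomised group and is open to bias of unknown sign and size

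*Protocol article*

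**What the plan says.** The Randomization section sends every eligible, consenting patient to allocation: "All patients who give consent to participate and who fulfill the inclusion criteria will be randomized". It adds: "The allocation ratio will be 1:1". According to the Blinding section, those who know the allocation include the treating osteopaths, "as well as patients and parents when the patient is under 18".

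The primary outcome is a change score: "We will calculate the difference between the fMAIA values between the last and the first evaluations". It is compared between groups with a Student or Mann-Whitney test, two-sided at 0.05.

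Statistical methods, Quantitative data, then sets the rule at issue: "Subjects randomized to a group that will ultimately do not join their randomization group will be out of the study". The same paragraph rules out adjusted or additional analyses on grounds of sample size. Its one safeguard is this: "We will compare the characteristics of dropout subjects compared to those who completed the study to investigate possible biases".

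A second text may also remove patients. The Non-inclusion criteria already bar entry where "they have a contraindication to osteopathic body approach sessions (fracture, recent surgery, etc" applies. A separate list headed Exclusion criteria returns to the subject: "Patients will be excluded from the research if (1) they have a contraindication to osteopathic body approach sessions". Its examples add a somatic state that does not suit the treatment. This list gives no time point and names no arm.

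**The concern.** A patient who has been randomised belongs to the comparison. Removing her because she did not take up her allocation makes the analysed groups depend on a choice or event that came after randomisation, and that may be related to how her interoceptive sensitivity would have changed.

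The two arms do not face the rule equally. Group B continues with usual care, which these patients already receive. Group A has five hands-on sessions to accept. With allocation known to patients and parents, non-uptake is more likely in group A. The Discussion itself expects ambivalence about treatment to be a difficulty.

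The stated aim is to show that adding osteopathy is significantly more efficacious than usual care, and the Discussion would use a positive result to argue for osteopathy as an additional option. A difference between selected groups supports that claim less well than a difference between randomised groups. If being out of the study also means that later questionnaires are not sought, no later analysis plan can recover the missing data.

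**Working it through.** **Is this a rule or an omission?** Set side by side, the Randomization section allocates all eligible consenting patients, and the Quantitative data section then drops some of them for not joining their group. No other section says that patients are analysed as allocated. So this is a stated rule, not a detail left to an analysis plan.

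**The plan's own figure.** The Sample size section wants more than 30 per group, allows 5–10% dropout and arrives at 36. Using N/(1−d):
- 31/0.90 = 34.4, rounded up to 35
- 32/0.90 = 35.6, rounded up to 36
- 31/0.95 = 32.6, rounded up to 33

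The stated 36 fits the 10% end. No arithmetic error is involved. A 5–10% loss leaves 34.2 to 32.4 of 36.

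**Size of the bias.** The documents give no non-uptake rate, no SD of change for the trial arms and no outcomes for removed patients, so everything below is assumed:
- f = share of group A removed, taken as 5–10%. This borrows the range of the overall dropout allowance; it is not a stated non-uptake rate.
- δ = how much less the removed patients would have changed than those retained, taken as 0.5–1 SD.
- no true effect, group B complete at 36, unit SD, normal approximation.

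The full group A mean is (1−f)·m + f·(m−δ) = m − fδ, where m is the retained mean. The retained mean is therefore too high by fδ. The standard error is √(1/[36(1−f)] + 1/36). The rejection rate is 1 − Φ(1.96 − fδ/SE) + Φ(−1.96 − fδ/SE).

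| f | δ (SD) | Shift fδ (SD) | SE | Rejection rate |
|---|---|---|---|---|
| 5% | 0.5 | 0.025 | 0.239 | 5.1% |
| 5% | 1 | 0.05 | 0.239 | 5.5% |
| 10% | 0.5 | 0.05 | 0.242 | 5.5% |
| 10% | 1 | 0.10 | 0.242 | 7.0% |

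In whole patients, with the same δ range:
- 2 removed: shift 0.03–0.06 SD, rejection 5.2–5.6%
- 4 removed: shift 0.06–0.11 SD, rejection 5.6–7.4%
- 6 removed: shift 0.08–0.17 SD, rejection 6.3–10.3%

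**Direction.** If removed patients would have done better (δ negative), the shift has the same size but favours usual care. If they do not differ, it is zero.

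**The Exclusion criteria.** Contraindication is screened at entry by the Non-inclusion criteria, and a compatible somatic state is an inclusion criterion. A further list under its own heading, with its own log of excluded subjects, most naturally describes removal after inclusion. That is a reading of the layout; the text does not say it.

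**The safeguard.** Comparing dropouts with completers can show whether they differ on recorded characteristics. It does not put the removed patients back, and it cannot show how they would have changed.

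**The case against.** The strongest reply is that the effect is small. Under moderate assumptions the false-positive rate moves from 5% to at most about 7%, the trial calls itself exploratory, and the authors foresaw the issue by planning to compare dropouts with completers. The modest size stands for those assumptions. It does not make the rule sound, because the number removed and their outcomes are unknown in advance.

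A reader might infer that the comparison is biased toward osteopathy. The documents do not support that as a fact: they say nothing about the outcomes of removed patients, and disappointed usual-care patients could leave as well. The Discussion's warning about burden covers assessments as well as treatment. That almost nobody can fail to join group B is likewise conjecture; greater non-uptake in group A is only the more likely pattern.

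A reader might also take it as settled that the Exclusion criteria remove patients after randomisation and only from group A. The list states no time point and its wording covers all patients. The same clinical service follows both arms and could learn of a fracture or somatic decline in either. Removal after inclusion remains the natural reading, but it is an inference.

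Finally, one could assume that the removed 10% are exactly the lowest on the outcome, which gives a shift of 0.195 SD and about 12% rejection. Nothing in the protocol suggests so extreme a selection.

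**Conclusion.** The point holds. The protocol fixes a removal rule that acts after randomisation, states no analysis by randomised group and plans nothing to offset the rule. The primary comparison is therefore open to bias. The bias plausibly favours osteopathy because only group A has a new treatment to take up under open allocation, but neither its sign nor its size can be derived from the documents.

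The working range is a shift of 0.025–0.10 SD with a false-positive rate of about 5–7%. It rests on three assumptions: removal from group A only, a 5–10% share, and a gap of 0.5–1 SD. The case for correction rests on the principle and on the low cost of doing so, more than on these figures. The timing and scope of the Exclusion criteria are unclear and need to be stated.

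**What to change.** Replace the removal sentence in the Quantitative data section with: *All randomised patients are analysed in the group to which they were randomised, whether or not they start or complete the sessions; T2 and T3 questionnaires are sought from everyone unless consent is withdrawn.*

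In the Exclusion criteria, state when they apply, reconcile them with the Non-inclusion criteria, and add that after randomisation they do not remove a patient from follow-up or analysis. Whether sessions go ahead for such a patient is a separate clinical matter.

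Report the patients who took up their allocation only as a supportive analysis. The dropout comparison can stay as description.

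The cost is a few sentences, some further questionnaires from patients who do not attend, and possibly a slightly diluted estimate. The target of 36 per group does not change. As recruitment has already begun, the change should be documented and the registry updated, as the protocol provides for modifications, and questionnaires should be sought where still possible from anyone already removed, unless consent was withdrawn.
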